### Economic evaluation

The health economic plan is to ascertain the NHS, personal and intangible costs involved in previously diagnosed patients versus what they might have required had they worn the device for a period of 1 month’s monitoring. We shall develop an early cost-effectiveness model that will describe both these pathways using the data collected in the study. The effectiveness measure is likely to be obtaining a definitive diagnosis but we shall also allude to quality of life with the disease as a secondary measure of effectiveness when appropriate. We expect the model to be robust using standard probabilistic sensitivity analysis and by obtaining resource use standardised units, values using standard NHS and other unit costs (PSSRU, 2020). We will also collect impacts on personal costs such as out-of-pocket costs, lost wages and income from time-off work and changes to longer-term productivity using standard average UK wage rates.

The economic study will also collect quality of life data using the EQ-5D (3-level) questionnaire to ascertain the short-term and longer-term impact of episodes of dizziness on quality of life. This will inform the design of future clinical trials as well as the preliminary economic model and play an important role in informing whether quality of life is impacted by the different methods of diagnosis.

Data will be collected at each point of patient contact during the monitoring period, collecting data on the resources used and any productivity losses by patients in the preceding days/weeks. Quality of life data using the EQ-5D will be collected at the beginning and at the end of the whole monitoring period. This will help determine the overall quality of life with and without and the frequency of attacks and whether the process of diagnosis itself confers any perceptible changes in quality of life. We shall follow the CHEERS checklist or the Consolidated Health Economic Evaluation Reporting Standards (Husereau, 2022 Drummond M *et al*) in our work.

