## Introduction

 Up to 30% of the general population have experienced dizziness significant enough to interfere with activities at some point over their lifetime.^1^ Dizziness can have many causes and it can often present in an episodic manner and frequently unpredictable, so patients present as ‘normal’ during examination interictally; furthermore, reporting of symptoms is imprecise.^2 3^ Although many balance tests are available, they only provide a snapshot of balance function in the absence of an acute attack.^2^ Patients will see up to five specialists before receiving a diagnosis^4^ and the treatments offered vary in terms of risk and invasiveness. Dizziness places a significant burden on health services.^5^

Dizziness is debilitating. The three most common causes of episodic vertigo include Ménière’s disease (MD), vestibular migraine (VM) and benign paroxysmal positional vertigo (BPPV). MD and VM are conditions which result in unpredictable and violent episodes of extreme rotational vertigo, lasting for several hours. Patients with BPPV experience shorter episodes, provoked by normal movement of the head such as with looking up. Dizzy attacks can cause patients to vomit and will leave them physically exhausted. It can take weeks to recover in full, making everyday activities impossible. Dizziness has a financial impact on patients taking frequent sick leave from work or time off to attend hospital appointments.^6^

Different treatment options are available for the three conditions of interest. Patients with MD may be treated with invasive injections into the middle ear which carry risk of infection, damage to the eardrum and hearing loss. Drugs for VM are not without risk and the process of identifying the correct drug is time-consuming. By contrast, BPPV is treated by a simple head manoeuvre, however, if the manoeuvre is done on a patient with an incorrect diagnosis it is likely to result in repeated and unpleasant symptom provocation without benefit. Delays before receiving the correct diagnosis and treatment prolong the suffering of patients, both in terms of the dizziness itself as well as the uncertainty of their prognosis and when the diagnosis is unclear patients may be offered treatments which are eventually revealed to have been for the incorrect condition. Therefore, there is a benefit in providing quick access to the correct condition-specific treatment.

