### Blinding

Blinding is not possible due to the design of the trial. Participant diagnosis is confirmed as part of the inclusion criteria, there are no separate arms of the trial and all participants will wear the device in the same manner. The primary outcome is objectively assessed.

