### Intervention

All participants fulfilling the eligibility criteria and providing consent will wear the CAVA device for up to 30 days. To balance the consequences of delaying BPPV treatment with not being able to identify the nystagmus associated with BPPV, individuals with BPPV will be offered a particle positioning manoeuvre after 4 days of wear. The CAVA algorithm will then diagnose each patient based only on the data recorded from the device. The accuracy of the system will be tested by comparing the CAVA system’s diagnosis with each patient’s known diagnosis. The results of the algorithm work (‘the diagnosis’) will not be available until the end of the trial and will not be made available to clinicians or patients during the trial.

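### In BPPV, the start-to-end EQ-5D change cannot separate device wear from the treating manoeuvre offered after 4 days, so it should not inform the process-of-diagnosis question

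*Protocol article*

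**What the plan says.** Protocol article, Economic evaluation, fixes the timing: "Quality of life data using the EQ-5D will be collected at the beginning and at the end of the whole monitoring period". It also fixes the purpose: these readings are to help show "whether the process of diagnosis itself confers any perceptible changes in quality of life". Earlier in that section EQ-5D is expected to "play an important role in informing whether quality of life is impacted by the different methods of diagnosis".

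Intervention has everyone wear the device for up to 30 days, and adds that "individuals with BPPV will be offered a particle positioning manoeuvre after 4 days of wear". The Introduction treats such a manoeuvre as the therapy for the condition: "BPPV is treated by a simple head manoeuvre".

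Three further statements bear on what a before-after change can mean. Blinding says "there are no separate arms of the trial" and "Participant diagnosis is confirmed as part of the inclusion criteria". Intervention says that the algorithm's diagnosis "will not be made available to clinicians or patients during the trial".

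**The concern.** A before-after difference supports a statement about the diagnostic process only if nothing else that is planned and likely to move quality of life happens between the two readings. In BPPV something does: the plan itself schedules an offer of treatment early in the interval. An EQ-5D gain in BPPV could then be credited to the diagnostic process when it came from the manoeuvre, or a burden from wearing the device could be hidden by relief from treatment.

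The article says that EQ-5D will feed the design of later trials and the preliminary economic model (Economic evaluation), and that the health economic study will inform the market access plan (Secondary outcomes). A misattributed change could travel into those outputs. The schedule is also something that a later analysis plan cannot repair, because a reading that was not taken before the manoeuvre cannot be recovered.

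**Working it through.** **Group sizes** (Recruitment and screening: 85 per condition, 255 in all). 3 × 85 = 255, which reproduces the plan's total. BPPV share: 85/255 = 33.3%. MD plus VM: 255 − 85 = 170. These are targets; up to 400 may be recruited, so the final counts may differ.

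**Where the manoeuvre falls.** EQ-5D covers the whole monitoring period, the device goes back at the end of 30 days (The CAVA device), and the manoeuvre is offered after day 4. With full wear, 30 − 4 = 26 days follow the offer, and 26/30 = 87% of the interval can be post-treatment. If wear stops at day D, the share is (D − 4)/D; for example, D = 10 gives 6/10 = 60%. It reaches zero only if the closing EQ-5D comes at or before the manoeuvre. The article does not say outright when that reading is taken for a BPPV participant who stops early, and the participant timeline figure is not available here. Treatment between the readings is therefore the likelier reading and not a certainty for every participant.

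**What the change contains.** Write w for the effect of wearing the device, n for natural course and regression to the mean, u for manoeuvre uptake and e for the mean EQ-5D effect in those who accept.

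- BPPV: mean change = w + n + u × e
- MD or VM: mean change = w + n′ + c, where n′ is that condition's own natural course and c is any concurrent treatment

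Two readings and one arm give one equation per condition. In BPPV, w cannot be separated from u × e. In MD and VM the manoeuvre term is absent, but w still cannot be separated from n′ and c.

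**What w can represent.** Participants enter already diagnosed and nobody sees the CAVA result during the trial. The only part of the CAVA process between the two readings is wearing the device, so in every condition the change reflects at most that.

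**Size.** The documents give neither u nor e. As an assumption only, take u from 0.5 to 1 and e from 0.02 to 0.20:

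- low end: 0.5 × 0.02 = 0.01
- high end: 1 × 0.20 = 0.20

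The BPPV shift spans a factor of 20 over this assumed range, so the size is unknown. The inability to separate the two terms does not depend on these values, provided that some participants accept and the manoeuvre has some effect.

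**The case against.** The case on the other side has four parts.

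**It is a matter for the analysis plan.** Reporting by condition and choosing which group carries the interpretation are details that an article commonly leaves to a later document, and the article says that a statistical analysis plan will follow. This stands for the reporting part. It does not stand for the two-reading schedule and its stated purpose, both of which the article fixes.

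**The aim is modest.** The article says only that the readings contribute to answering the question. It makes quality of life a secondary effectiveness measure, with a definitive diagnosis as the likely main one. It promises no causal estimate of device wear. This stands, and it lowers the severity.

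**The weakness is not specific to BPPV.** All three conditions lack a comparator. Entry requires at least two episodes in the preceding 4 weeks (Population), which invites regression to the mean, and the listed criteria do not rule out concurrent MD or VM treatment. This stands in full. A reader might infer that MD and VM give a clean estimate once BPPV is set aside; they give only a less confounded one. What BPPV adds is a known treatment that the protocol itself schedules.

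**Treatment belongs to the pathway.** The manoeuvre follows from the diagnosis that the participant already had, not from the CAVA result, so its benefit cannot be credited to the CAVA process. This objection fails.

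A reader might also infer that the manoeuvre contaminates a quality-of-life result pooled over all three conditions. The article does not say that EQ-5D will be pooled, so that reading is not supported.

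**Conclusion.** The point holds in a limited form and is minor. In BPPV participants who accept the manoeuvre, the start-to-end EQ-5D change cannot separate device wear from treatment, and it should not be used for the process-of-diagnosis question. It concerns one third of the planned sample (85 of 255). The size of the shift is u × e and is unknown.

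The conclusion rests on the closing EQ-5D coming after the manoeuvre, which the text supports but does not state for participants who stop early, and on some uptake and some effect of treatment.

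A reader might go further and conclude that the EQ-5D data are worthless or that the diagnostic accuracy result is compromised. The documents support neither. The EQ-5D readings keep their descriptive and modelling uses if they are labelled correctly. The primary outcome is derived from nystagmus recordings and does not use EQ-5D.

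**What to change.** 1. Report EQ-5D change by condition. Do not use the BPPV start-to-end change for the process-of-diagnosis question, and describe it as including treatment.
2. For BPPV participants still to enrol, add one short EQ-5D at the contact just before the manoeuvre and record the manoeuvre date. Report that change separately, since it covers roughly 4 days and not up to 30.
3. State that the MD and VM change is also an uncontrolled before-after change, open to regression to the mean and to any concurrent treatment. State too that it reflects at most device wear, because participants are already diagnosed and the CAVA result is withheld.

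The offer of treatment after 4 days stays as it is.

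The cost is one brief extra questionnaire and one recorded date for later BPPV participants, plus some wording. The process-of-diagnosis reading then rests on 170 planned participants. Compared with an analysis of all 255, which the article does not specify, and assuming the same standard deviation in each condition, the confidence interval would be √(255/170) = 1.22 times as wide. Item 2 brings nothing if BPPV recruitment is already complete; items 1 and 3 can still be done.

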### Commercialisation

A commercialisation consultant will oversee a portfolio of work to support the commercialisation of the CAVA system. They will produce a market access plan detailing CAVA’s route to commercialisation and confirm CAVA’s placement within existing NHS pathways and how it would be implemented. We will build on our previous focus-group work with a stakeholders’ event involving professionals, patients and IT stakeholders from NHS organisations. We will identify the issues important to stakeholders regarding the feasibility of adoption within the NHS and will establish support for adoption. We will host a public event to review the interim findings from the trial and a public dissemination event to share our findings with the public. Throughout the project, we will engage with prospective licensees.

### Data management and monitoring

All data (except data recorded on to the device itself) is collected and managed using REDCap,^24 25^ a secure web-based software platform designed to support data capture for research studies, providing audit trails for tracking data collection and manipulation and automated export procedures to common statistical packages.

Oversight of the trial and data collected is by the TMG and other independent committees, each with their own remit and terms of reference.

CAVA trial team members monitor the trial database and generate reports and review data entry. The essential trial issues, events and outputs, including defined key data points, are discussed by the trial team on a weekly basis and with relevant committees when necessary.

## Ethics and dissemination

This study has been approved by the West Midlands—South Birmingham Research Ethics Committee and the MHRA (REC reference: 22/WM/0229, IRAS Project ID: 317899, MHRA: CI/2022/0062/GB, Clinical Investigation Plan (CIP) V.3.1 dated 25 January 2024). Study sites are included in the application and do not need to obtain separate ethics approval. Participants provide consent to take part and the right of refusal to participant or requests of withdrawal will be respected.

Dissemination plans include publication in peer-reviewed journals, presentations at academic and public conferences consisting of patients and the public and to policymakers and practitioners. The results of the trial will be disseminated regardless of the direction of effect. The statistical analysis will be drafted and approved by the trial’s governance committees prior to data lock. The CAVA systems route to commercialisation will be developed using study outputs as well as data from consultation with stakeholders regarding the feasibility of adoption within the NHS, from PPI meetings and public dissemination events.

### Current study status

The first participant was randomised in February 2023. Recruitment is expected to take 24 months with results expected to be published following the final device return in 2025.
